#### Outcome measures

Outcomes are the number of participants using Vertigo Training (Reach), the number of participants finishing the exercise regimen (Implementation), and the descriptive characteristics of these participants (Reach). We will also evaluate characteristics associated with successful treatment (Effectiveness). Successful treatment will be defined as a change of 3 points or more in the VSS-SF score between baseline and 3 months, which indicates a clinically relevant difference in vestibular symptoms.

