## Phase 2: nationwide implementation of Vertigo training

We will embed Vertigo Training in Dutch primary care from April 2023 onwards. The online application will be made freely available through the website www.gezondheidsmeter.nl. More information on Vertigo Training is described in Table 3.

**Table 3 Tab3:** Information on intervention to be implemented: Vertigo Training

Vertigo Training is a freely accessible internet-based intervention that contains six exercises. These six exercises include eye, head, and body movements that aim to stimulate vestibular compensation, a process in which the nervous system reorganises and is able to overcome damage of the vestibular system. In addition, a form of exposure-based behavioural therapy takes place by deliberately provoking vestibular symptoms in a controlled environment. The application prescribes a personal exercise regimen based on the severity of symptoms while performing the exercises. Patients are asked to perform the exercises twice a day for 10 min. The regimen lasts 6 weeks. Patients can start with Vertigo Training on their own initiative, or they can be referred to the treatment by a healthcare provider. They can perform the exercises by themselves, but it is also possible to receive support from a healthcare provider, such as a physiotherapist. In the Netherlands, patients can access physiotherapy through self-referrals.
Patients are eligible for Vertigo Training if they are 18 years and older, if they have had vestibular symptoms for at least one month during most days of the week, and if these symptoms are provoked or exacerbated by head movements or visual stimuli.

We created an implementation plan, involved local implementation specialists, and identified relevant stakeholders (i.e. GPs, ENT specialists, physiotherapists, and patients with vestibular symptoms) to adapt our implementation strategy to their needs. The final strategy consists of the following components: guideline adaptations; mass and target marketing strategy; pharmacotherapeutic audit and feedback meetings (PTAMs); education for GPs, patients, and physiotherapists; clinical decision support; and local champions. We will elaborate on these components further on.

We used the Standards for Reporting Implementation Studies (StaRI) Statement to report the implementation strategy and the intervention (Additional file 3) [31].

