### Prospective observational cohort study

#### Study design and data collection

We reported this prospective observational cohort study in line with the The Strengthening the Reporting of Observational Studies in Epidemiology (STROBE) Statement (Additional file 4) [25]. During the implementation period (April 2023–March 2025), we will gather data from participants who use Vertigo Training and who give informed consent for the collection and analysis of their data. Participants who do not give informed consent can still use the application. We will evaluate the usage of Vertigo Training and the characteristics of participants. The evaluation will take place on a regular basis and we will adapt our implementation strategy accordingly. We will also determine whether certain characteristics are associated with successful treatment.

Data on the usage of Vertigo Training will be collected. We will also gather data on demographic characteristics, diagnosis and treatment of vestibular symptoms, and severity of vestibular symptoms according to the vertigo symptom scale-short form (VSS-SF) [36], using an online voluntary questionnaire at baseline. The VSS-SF will additionally be evaluated at 6 weeks, 3 months and 6 months. Table 4 shows an overview of variables.

**Table 4 Tab4:** Overview of variables for prospective observational cohort study

Variable	Definition
Age	In years at time of start intervention
Gender	Male, female, other
Place of residence	-
Diagnosed vestibular disorder	Anamnestic
Education level	Primary education, prevocational secondary education, senior general secondary education, pre-university education, senior secondary vocational education, higher vocational education and university education
Migration background	Yes (if at least one parent was born abroad) or no
Received medical care for vestibular symptoms	Yes (from general practitioner, medical doctor at hospital, medical doctor at other type of clinic, physiotherapist, and/or other healthcare provider) or no
Prescription for anti-vertigo drug in past	Yes or no
Vestibular symptoms	According to vertigo symptom scale-short form at baseline, 6 weeks, 3 months, and 6 months
Acquaintance with Vertigo Training	Through the patient association, the internet, a healthcare provider, friends, social media, and/or other ways

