#### Analysis

Descriptive statistics will be used to assess the usage and characteristics of participants. In addition, we will perform a mixed-effects logistic regression analysis to evaluate whether these characteristics are associated with successful treatment. We will use IBM SPSS Statistics (version 28.0) for the descriptive statistics and the mixed-effects logistic regression analysis will be performed with R software (version 4.2.1).

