The main strength of this study lies in its employed research methods. For the evaluation of the implementation, we will carry out both an interrupted time series and a prospective observational cohort study. An interrupted time series is considered the strongest design to evaluate the effect of an intervention when a RCT is not feasible [33]. By additionally employing a qualitative research method, we can enrich the evidence. Furthermore, by regularly analysing prospective data from Vertigo Training and identifying barriers and facilitators, we can tailor our implementation strategy and increase the effectiveness of our implementation. Lastly, we will use routine primary care data from more than 1.2 million patients registered at general practices throughout the Netherlands in addition to data from participants using Vertigo Training. This supports the generalisability of our results. There are also methodological limitations to this study. As the effectiveness of the individual components of our strategy will be evaluated with an interrupted time series on general practice level, we have to make several assumptions. For instance, when one GP from a general practice with multiple GPs will attend a PTAM, we assume that this GP will have an impact on all patients who are registered at that general practice. This will have an influence on the estimation of the effectiveness. In addition, it will not be feasible to determine for all components whether or not general practices are exposed. We will, for example, not be able to separate who has been exposed to the mass marketing strategy and who has not been exposed. We are therefore restricted in measuring whether exposure to a specific component resulted in a change in outcomes. Furthermore, as patients can also perform the exercises using the patient platform Thuisarts.nl, it may be possible that only a selected group (e.g. patients with advanced digital skills) will use Vertigo Training, introducing bias into our data. We will not be able to gather data from patients using Thuisarts.nl to increase the validity of our results. Another consequence of this is that we cannot tailor our strategy to the needs of this specific patient group. The same accounts for patients with vestibular symptoms that would have an indication for Vertigo Training, but were not referred to the treatment and/or did not start the treatment. Lastly, Vertigo Training has broad inclusion criteria. Therefore, some participants might benefit less from the intervention than others. For example, the Epley manoeuver is more effective in patients with benign paroxysmal positional vertigo than VR in the short term [11]. This might influence the estimation of the effect of Vertigo Training.

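### Success is a fixed 3-point VSS-SF change with no entry minimum and no control group, so baseline severity will appear to predict success even if the treatment does nothing

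*Protocol article*

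**What the plan says.** All references are to the protocol article, Phase 3, Prospective observational cohort study, unless stated otherwise.

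- **Outcome measures.** The responder rule is: "Successful treatment will be defined as a change of 3 points or more in the VSS-SF score between baseline and 3 months". The threshold is justified as one "which indicates a clinically relevant difference in vestibular symptoms". It is the same for every participant, and the sentence gives no direction of change. The result is labelled Effectiveness.
- **Analysis.** A mixed-effects logistic regression is used "to evaluate whether these characteristics are associated with successful treatment". The article does not say whether baseline VSS-SF is a predictor, an adjustment term or neither.
- **Study design and data collection.** The cohort is defined thus: "we will gather data from participants who use Vertigo Training and who give informed consent for the collection and analysis of their data". There is no comparison group. Table 4 lists vestibular symptoms among the variables: "According to vertigo symptom scale-short form at baseline, 6 weeks, 3 months, and 6 months".
- **Phase 2, Table 3.** Eligibility rests on adult age, on duration and frequency ("if they have had vestibular symptoms for at least one month during most days of the week") and on provocation ("if these symptoms are provoked or exacerbated by head movements or visual stimuli"). No VSS-SF minimum is given.
- **Discussion.** The authors concede: "Vertigo Training has broad inclusion criteria. Therefore, some participants might benefit less from the intervention than others". Floor effect and regression to the mean are not mentioned.

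**The concern.** The baseline score enters the outcome directly, because success is baseline minus follow-up reaching a fixed number of points. Two artefacts follow when success is related to baseline severity. A participant close to the bottom of the scale has no room to fall by 3 points. A participant who enters during a bad spell tends to drift back to the usual level and is counted as a success without any help from the treatment. No control group shows how much of this would have happened anyway.

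The analysis may therefore report that more severe patients respond better to Vertigo Training. Under an Effectiveness label that would be read as a finding about who benefits, although the definition alone can produce it.

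**Working it through.** The article gives no expected success rate, sample size or VSS-SF distribution for this cohort, so there is no stated figure to reproduce.

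**Inputs from the article:** threshold of 3 points; baseline to 3 months; no entry minimum; no control group.

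**Assumptions (not in the article):** scores rounded and cut to 0-60; baseline mean 14, SD 9; correlation r between baseline and 3 months of 0.5, 0.6 or 0.8; no true change; change means a decrease.

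**Step 1: the floor.** A fall of 3 from a score of 0, 1 or 2 would end below 0, so success there is 0%. The share of such participants is P(rounded score of 2 or less) = Φ((2.5 − 14)/9) = Φ(−1.28) ≈ 0.10. With skewed (gamma) severity and baseline mean/SD of 8/6, 12/8 or 16/10, the share is 5-17%.

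**Step 2: regression to the mean by hand.** Given baseline b, the expected 3-month score is 14 + r(b − 14), with SD 9√(1 − r²). For r = 0.6 the SD is 7.2.

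- b = 5: expected 8.6; success needs 2 or less; Φ((2.5 − 8.6)/7.2) ≈ 0.20.
- b = 23: expected 19.4; success needs 20 or less; Φ((20.5 − 19.4)/7.2) ≈ 0.56.

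**Step 3: simulation by baseline quarter, no true change.**

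| r | Lowest | Second | Third | Highest |
|---|---|---|---|---|
| 0.5 | 12.6% | 31.8% | 46.0% | 66.0% |
| 0.6 | 13.2% | 31.7% | 43.6% | 61.6% |
| 0.8 | 13.9% | 29.1% | 36.9% | 49.0% |

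At r = 0.6 the odds ratio of highest against lowest quarter is (0.616/0.384)/(0.132/0.868) ≈ 10.5. At r = 0.5 and 0.8 it is about 13.5 and 6.0. Under the gamma model with reliability 0.70 or 0.85 and no effect, the quarters show 7-16% against 32-55%. The gradient is somewhat smaller there but has the same direction.

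**Step 4: another characteristic with no effect of its own**, whose carriers score about 6.9 points higher at baseline.

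- *Difference partly fades.* The characteristic tracks the score at entry, so the 3-month difference is r × 6.9 = 3.5, 4.1 or 5.5. The unadjusted odds ratios are 2.06, 1.94 and 1.69. Adjustment for baseline returns them to about 1 (0.99-1.02 in a run with a 6.8-point difference).
- *Difference lasts in full.* The unadjusted odds ratio is 1.09-1.11. Linear adjustment for baseline moves it to 0.45-0.63, and restriction to baseline 3 or above moves it to 0.85-0.89.
- *Gamma model, characteristic linked to true severity only.* Unadjusted, the odds ratio is 1.00-1.04 with no effect and 1.03-1.08 with a constant effect. It is 1.27-1.43 with a 30% proportional effect, where the larger absolute gain in severe cases is partly real. After linear adjustment it is 0.74-0.85.

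**Step 5: the missing direction.** Across the gamma scenarios, with and without a treatment effect, 7-37% of participants worsen by 3 points or more. Read literally, they meet the definition of success.

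**The case against.** The strongest reply has four parts.

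1. *Covariates are left to the analysis plan.* This stands. The article names no covariates, an analysis plan not shown may do so, and the absence of baseline adjustment here is no finding. It does not answer the point, which concerns a definition that the article does fix: no covariate list changes who can meet it or removes the baseline score from it.
2. *The floor may affect few people.* This stands in part. Symptoms on most days for at least a month probably make scores of 0-2 uncommon. Neither the scale range nor the score distribution is in the article, so the 5-17% is assumed. The gradient in Step 3 does not rest on those participants alone.
3. *Lasting traits are hardly affected.* This stands. A reader might infer that any group scoring higher at baseline will falsely appear to respond better. The article does not support that. Age, gender, education and migration background are lasting traits whose baseline difference can be expected to persist, and Step 4 then gives about 1.1. Received medical care, or learning of the application from a healthcare provider, could plausibly track a bad spell at entry, but the article does not show that they do.
4. *The obvious remedies can do harm.* This also stands. Compulsory baseline adjustment, or restriction to baseline 3 or above, can reverse the bias for lasting traits, so neither should become the primary rule.

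In addition, a fixed clinically relevant change is a conventional responder rule, and this is a secondary association analysis: the primary outcome of the interrupted time series is VR referrals.

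**Conclusion.** The concern holds for baseline severity. With a fixed 3-point threshold, no entry minimum and no control group, measured baseline VSS-SF is tied to success by construction. Under the main assumptions an inert treatment gives 13-14% success in the lowest baseline quarter and 49-66% in the highest. The exact size depends on the assumed mean, SD, correlation and floor of 0; the direction was the same in every setting tried.

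For the other characteristics it is only a possibility: an odds ratio of about 1.7-2.1 if a 7-point baseline difference partly fades by 3 months, and about 1.1 if it lasts.

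A reader might also infer that low scorers in general cannot succeed. That applies only to scores of 0-2, and only if change means improvement, which the context suggests but the sentence does not say.

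The point should be corrected because the result is meant to say for whom the treatment works. It does not touch the primary outcome.

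**What to change.** 1. State that success is a decrease of at least 3 points.
2. State that the association of baseline VSS-SF with success will not be interpreted as a predictor of benefit, and that this uncontrolled cohort cannot separate benefit from regression to the mean.
3. Report how many participants score below 3 at baseline, and give results for those at 3 or above as a sensitivity analysis. This concerns the analysis only, not who may use the application.
4. Report the other characteristics both without and with baseline VSS-SF (modelled flexibly, not only as a straight line), alongside an analysis of the 3-month VSS-SF as a continuous outcome. Note that baseline adjustment can reverse the bias for lasting traits, so a disagreement between the two results is to be reported as uncertainty.

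All scores needed are already to be collected. The cost is a few sentences, a little more analysis and a weaker statement about who benefits.

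### The cohort's only stated analysis of who benefits reduces the VSS-SF to a yes/no 3-point change at 3 months, which costs at least about 36% of the information on each association if change is roughly normal

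*Protocol article*

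**What the plan says.** All of this is in the protocol article, Phase 3, Prospective observational cohort study.

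- *Study design and data collection*: the VSS-SF is part of a voluntary online questionnaire at baseline. "The VSS-SF will additionally be evaluated at 6 weeks, 3 months and 6 months". Table 4 lists the same four time points.
- *Outcome measures*: "We will also evaluate characteristics associated with successful treatment (Effectiveness" is named after usage, completion and participant description. Then: "Successful treatment will be defined as a change of 3 points or more in the VSS-SF score between baseline and 3 months". The reason given for the threshold is that it is a change "which indicates a clinically relevant difference in vestibular symptoms".
- *Analysis*: "we will perform a mixed-effects logistic regression analysis to evaluate whether these characteristics are associated with successful treatment". No random effect or cluster is named.

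No analysis of the VSS-SF as a numeric score is described. No cohort size, SD, expected success share or power is given. I read change as improvement; the wording does not give a direction, which is a separate matter.

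**The concern.** The outcome, cut-off, visit and model family are all stated, so this is a choice the article has made and not a detail left to a fuller plan. Under that choice a 2-point gain counts the same as a worsening, and a 3-point gain the same as a 15-point gain. Two of the three follow-up scores are collected but do not enter the success definition.

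This is the only stated quantitative analysis of who benefits. The Discussion expects benefit to vary because the inclusion criteria are broad. Table 4 offers many candidate characteristics, some with several categories (seven education levels, for example), and lost precision hurts most in small categories. Real differences would be easier to miss, and the result would describe who crosses 3 points but not how much each group improves.

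The stated model also does not fit the stated outcome. With one binary value per participant, the variance of a participant random effect cannot be identified, and no other grouping is given.

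**Working it through.** The article has no figure of its own to reproduce. Everything below rests on assumptions, shown with ranges.

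**1. Information lost by the cut.** For a roughly normal change score with a share p classed as success, the loss relative to the full score is

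loss = 1 − φ(z_p)² / [p(1 − p)],

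where z_p is the normal quantile of p and φ the normal density.

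| Success share p | φ(z_p)² | p(1 − p) | Loss |
|---|---|---|---|
| 50% | 0.1592 | 0.25 | 36.3% |
| 40% or 60% | 0.1493 | 0.24 | 37.8% |
| 30% or 70% | 0.1209 | 0.21 | 42.4% |
| 20% or 80% | 0.0784 | 0.16 | 51.0% |
| 10% or 90% | 0.0308 | 0.09 | 65.8% |

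Under normality 36% is the minimum. The loss passes 50% once the share falls below about 21% or rises above about 79%. For an assumed mean improvement of 1 to 6 points and SD of 4 to 8, it is 36–48%.

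**2. Check by sample size.** Assume two equal groups 0.2 SD apart, two-sided 5%, 80% power. The score needs 393 per group. The yes/no outcome needs 618 (p = 50%), 684 (30% or 70%) or 805 (20% or 80%). The implied losses, 1 − 393/618, 1 − 393/684 and 1 − 393/805, are 36.4%, 42.5% and 51.2%.

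**3. Check by simulation.** With whole-number change scores and 400 participants, the loss was 35–41% for success shares of 40–66% and 55% at 82%.

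**4. The unused visits.** If three follow-up change scores are equally correlated (ρ), their mean has (1 + 2ρ)/3 of the variance of one. At ρ = 0.5 this is 0.667; at ρ = 0.8 it is 0.867. Against the three-visit mean, the single-visit cut keeps 0.637 × 0.667 = 42% to 0.637 × 0.867 = 55% of the information at p = 50%. At p = 20% it keeps 0.490 × 0.667 = 33% to 0.490 × 0.867 = 42%. This assumes a difference of similar size at all three visits.

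**5. What it means for power.** Assume SD 8, baseline correlation 0.5, a 2-point difference and two equal groups. The baseline-adjusted residual SD is 8 × √(1 − 0.25) = 6.93, so z = 2√n / (2 × 6.93). Baseline-adjusted simulation at n = 400 gave 82–83% power for the score and 55–60% for the cut, a relative efficiency of about 0.52–0.60. Carrying that forward, with power = Φ(z√efficiency − 1.96):

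| n | z | Score | Cut |
|---|---|---|---|
| 400 | 2.89 | 82% | 55–61% |
| 1,000 | 4.56 | 99.5% | 91–94% |
| 1,500 | 5.59 | about 100% | 98–99% |
| 2,000 | 6.45 | about 100% | above 99% |

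For a 1-point difference at n = 1,500, z halves to 2.80, and power is 80% for the score against 52–58% for the cut. The relative loss does not depend on n; whether it matters for power does.

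**The case against.** The other side has a fair case. The threshold is prespecified, tied to one time point and justified as clinically relevant. A responder analysis answers the literal question of which characteristics go with success, whereas a model of mean points answers a neighbouring one. The analysis is not primary: the named primary outcome is the VR referral rate in the interrupted time series. The application is free, nationwide and observed for two years, so a cohort well above 1,000 is plausible, and a 2-point difference would then be found either way.

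Most of this stands, and it rules out several stronger readings that a reader might infer:

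- *That the analysis is underpowered.* The article gives no cohort size, SD or success share, so this cannot be shown.
- *That the loss is a fixed 36–50%.* It depends on normality and on an unstated success share; 36% is a floor under normality and 50% is not a ceiling.
- *That a participant without a 3-month score contributes nothing, or that the associations are biased.* The success definition gives such a person no observed value, but missing-data handling is commonly left to a fuller plan. Bias would also require that early response affects who returns the 3-month form, on which the article is silent.
- *That 3 points is the wrong threshold, or that a responder result has no place.* Nothing in the article supports this.

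One part does not answer the point. A threshold that helps to read one person's result is no reason to discard the rest of the scale when estimating associations. Nor does the mixed-effects label show that repeated scores enter the model, because the outcome is defined at 3 months only.

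**Conclusion.** The concern holds as a matter of efficiency and fit, not as an error that invalidates the study. If change in VSS-SF is roughly normal, the stated outcome discards at least about 36% of the information on each association, and more as the success share moves away from one half (51% at 20% or 80%, 66% at 10% or 90%). Leaving out the other two follow-up scores adds to this under the correlations assumed above. The consequence for power ranges from more than 20 percentage points at 400 participants to almost nothing for a 2-point difference at 1,500 or more; smaller differences reopen the gap. Separately, the *Outcome measures* and *Analysis* sections do not fit together, because a mixed-effects model is named for one binary value per person with no clustering stated. The change is worth making because it is cheap and the relative loss holds at any cohort size.

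**What to change.** In the cohort's *Analysis* section, estimate the associations with a linear mixed model of VSS-SF at 6 weeks, 3 months and 6 months. Adjust for baseline VSS-SF and visit, and include a random intercept per participant, which gives the mixed model a purpose. Include everyone with a baseline score and at least one follow-up score. Report the adjusted 3-month difference for each characteristic. Limit interactions between characteristic and visit to what the data support, for example by collapsing sparse categories.

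Keep the 3-point responder analysis at 3 months alongside it for clinical interpretation. If it remains a mixed-effects logistic model, name the cluster; otherwise call it ordinary logistic regression.

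Cost: a change of wording and some programming in R, which is already planned, with no new data or visits. The downside is that the results are in VSS-SF points and not odds of success, and that the model assumes roughly normal residuals for a bounded score. The retained responder analysis covers the first; robust or bootstrap standard errors can address the second.
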